## Abstract

**Background:**

Cardiac biomarkers are important components for diagnosing perioperative myocardial infarction (MI). Efforts to detect MI by biomarker-release only faced heavy criticism, because cardiac biomarker-release has also been observed in situations that are not always related to cell death (e.g., renal insufficiency, neurological diseases, and even after endurance exercise). This study correlates release patterns of all three classically used cardiac injury biomarkers (CK/CK-MB, Troponin T and I) with myocardial damage visualized by late gadolinium enhanced cardiac magnetic resonance imaging (LGE-cMRI) and also compares biomarkers among each other.

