#### Primary objective

2.2.1

The primary objective of the study is to assess whether the perioperative releases of TnI, TnT, CK, and CK-MB correlate with myocardial damage, visualizable by LGE-cMRI. The primary endpoint is the correlation of the peak value of the respective biomarker with the amount of perioperatively induced myocardial damage quantified by LGE-cMRI.

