### Statistical considerations and methods

2.10

The statistical approach for the RORSCHACH study is exploratory and essentially descriptive. As mentioned previously, the primary endpoint is the correlation (Spearman's ρ) of the peak value of the respective biomarker (TnI, TnT, CK, CK-MB) with the amount of perioperatively induced myocardial damage quantified by LGE-cMRI. In addition, adequate methods of descriptive statistics to summarize biomarker distributions, exploratory bivariate correlation analyses (Spearman's ρ) and regression modeling (mixed, general linear models) including sensitivity analyses (e.g. stratified by study center) will be performed. There will be no adjustment for type I error.

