### Sample Size

2.11

With 85 evaluable patients, who are considered recruitable for practical reasons, α = 0.05 and a power = 0.8 for the primary endpoint H1: ρ = 0 against H0: ρ = 0.3 can be detected. Assuming a drop-out rate of 15 %, the required number of patients to be included is 100.

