## Discussion

3

The RORSCHACH trial will deliver the first comparative and quantitative information on the predictive value of the three classic cardiac injury markers used for the detection of new perioperative irreversible injury/MI in cardiac surgery.

Cardiac biomarkers are essential tools for diagnosing perioperative MI, yet their specificity remains contentious. We had discussed the inadequacy of defining MI solely based on biomarkers before [3]. A thorough comparison between different biomarkers after cardiac surgery and the quantitative relation to myocardial damage is lacking. The topic has raised substantial attention with several prominent publications [[6], [7], [8]] attempting to define cut-off values for the detection of MI by biomarker release only. While it is clear, that every true MI will cause the release of the proteins used for MI detection (specifically if it is a larger infarction), at low to intermediate amounts of biomarker release, it is not clear which pathophysiology is associated with the release observation. Since these intermediate values are most frequent, it is important to provide clarity, especially since MI definitions based on biomarker release only have been and still are used [[6], [7], [8]] for determining trial endpoints, in which surgery is compared to less invasive treatment modalities. Since biomarker release may also be associated with surgical stress, without being directly related to myocardial injury, this possibility may introduce a significant bias into the interpretation of trial results.

Although CAD patients were excluded, intraoperative factors such as severe hypotension or high-dose vasopressor use could lead to myocardial injury independent of the surgical procedure, which are residual confounders which can be hardly addressed quantitatively. For this reason, patients who develop clear cases of intraoperative shock requiring resuscitation doses or similar interventions will be subject to separated analyses.

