With RORSCHACH, we are going to deliver the first comparative and qualitative information on the predictive value of the classic cardiac biomarkers for the detection of new perioperative irreversible injury/MI in the heart surgery setting. Demonstrating this laboratory and radiological correlation would be one of the first evidence-based steps forward in optimizing the diagnosis of truly significant clinical events in patients after cardiac surgery. This trial will generate important information with significant implications for not only daily practice but importantly for the design of new clinical trials involving coronary artery disease.

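### The article promises a comparison of the biomarkers, but its stated analysis and sample size rest on one separate correlation per marker, which gives no valid uncertainty for a difference between markers

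*Protocol article*

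**What the plan says.** The comparison is promised in two places. The Abstract (Background) adds it to the correlation aim: "and also compares biomarkers among each other". Section 3 (Discussion), like the Discussion paragraph of the Abstract, makes it the deliverable: "The RORSCHACH trial will deliver the first comparative and quantitative information on the predictive value of the three classic cardiac injury markers".

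The formal parts ask something else. The primary objective (section 2.2.1) is "to assess whether the perioperative releases of TnI, TnT, CK, and CK-MB correlate with myocardial damage". Section 2.10 states that "the primary endpoint is the correlation (Spearman's ρ) of the peak value of the respective biomarker (TnI, TnT, CK, CK-MB") with the MRI-quantified damage. It adds descriptive summaries, exploratory bivariate Spearman correlations and mixed or general linear models. It labels the approach exploratory and leaves type I error unadjusted. Section 2.11 justifies 85 evaluable patients by "α = 0.05 and a power = 0.8 for the primary endpoint H1: ρ = 0 against H0: ρ = 0.3 can be detected", and allows 15% drop-out to reach 100. The secondary endpoints (sections 2.2.2 and 2.9) are perioperative complications. Section 2.7 mentions comparing the markers' kinetics.

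The article names no contrast between two markers' correlations with damage, and no precision for one.

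**The concern.** All four correlations come from the same patients and share one MRI outcome, so the estimates are dependent. A test of each against 0 says nothing about how precisely a difference between two of them is known. One marker reaching significance while another does not is not evidence that they differ. Judging by whether the separate intervals overlap is also wrong, because it ignores the covariance.

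At stake is the comparative statement that the Discussion promises. With only four separate results to hand, chance differences between equally good markers could be reported as a ranking.

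**Working it through.** **1. Reproduce the plan's figure.** Inputs from section 2.11: alpha 0.05 (two-sided assumed, since it reproduces the figure), power 0.80, rho 0.3 against 0. The hypothesis labels are swapped in the text, which is a separate matter. By Fisher's z:

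n = ((1.960 + 0.842) / atanh(0.3))² + 3 = (2.802 / 0.3095)² + 3 = 84.9, so 85.

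85 / (1 − 0.15) = 100. Both figures reproduce, for one correlation against zero. No between-marker quantity enters.

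**2. What four separate tests show when the markers are equal.** Simulation with 20,000 trials, n = 85, multivariate normal data, every marker–damage correlation 0.30 and equal inter-marker correlation. The inter-marker value is an assumption, shown as a range. A mixed result means at least one marker significant and at least one not.

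| Inter-marker correlation | 0.5 | 0.7 | 0.8 | 0.85 | 0.9 |
|---|---|---|---|---|---|
| Mixed result | 48% | 38% | 31% | 28% | 22% |
| Mean gap, highest minus lowest rho | 0.16 | 0.12 | 0.10 | – | 0.07 |

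The true gap is zero throughout.

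**3. Sensitivity to the common true correlation.** For inter-marker correlation 0.5 / 0.7 / 0.9, the mixed-result rate is:
- 16% / 13% / 8% at a true correlation of 0
- 60% / 47% / 28% at 0.2
- 14% / 11% / 7% at 0.4 (about 9% at inter-marker 0.85)
- about 1% at 0.5

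**4. Precision of a paired difference.** The simulated SD of the difference between two Spearman rhos (both truly 0.30, n = 85) is 0.107 / 0.084 / 0.061 at inter-marker correlation 0.5 / 0.7 / 0.85. Multiplying by 1.96 gives 95% half-widths of 0.21 / 0.16 / 0.12. Treating the two correlations as independent would give an SD of about √2 × (1 − 0.3²)/√82 = √2 × 0.100 = 0.142. The separate analyses therefore also misstate the precision.

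**5. What 85 patients can separate.** Power of a paired test for dependent correlations (Meng–Rosenthal–Rubin; simulated size 5.0% to 5.1%), at inter-marker correlation 0.5 / 0.7 / 0.8 / 0.9:
- 0.3 against 0.5: 49% / 69% / 85% / 99%
- 0.3 against 0.4: 16% / 21% / 29% / 50%

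**6. Multiplicity of the pairs.** Four markers give 4 × 3 / 2 = 6 pairs. With equal markers and equal inter-marker correlation, some unadjusted 95% interval excludes 0 when the range of four estimates exceeds 1.96 × √2 = 2.77 standard units. The studentized range gives 20.3% for that, and simulation at n = 85 gave 20% to 21%.

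**The case against.** The strongest case against has three parts.

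- **The comparison is secondary and the study is exploratory.** The primary objective is correlation, the analysis answers it, and the sample size reproduces. Section 2.7 speaks of comparing kinetics, which the descriptive summaries and mixed models can serve. This stands: a descriptive comparison is supported, and comparison should not be called the main aim.
- **The contrast may be in a plan that is not shown.** A journal article commonly leaves such detail to the full protocol or analysis plan. This stands in part. What remains is visible in the article itself: the promised comparison does not match the stated analysis, and 85 was justified for a different question.
- **Nobody says markers will be ranked by p-value.** True, so the mixed-result rates measure the risk of one way of reading the results, not a planned step.

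Stronger readings are tempting and should be resisted. A reader might infer that the trial cannot order the markers at all, or that a false ranking is likely whatever the truth. The rhos can be ordered, and mixed results become rare once the true correlations are near 0.5. A reader might also infer that the predictive-value wording obliges an ROC analysis. The endpoint is the amount of damage and the Discussion pairs that wording with a quantitative aim, so dichotomising is a preference. Finally, "importantly for the design of new clinical trials involving coronary artery disease" might be read as a conclusion about coronary patients. It claims only implications for trial design, and excluding coronary disease is deliberate (section 2.3).

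**Conclusion.** The point holds as a mismatch between the comparison promised and the analysis and sample size stated. It should be corrected, but it does not undermine the primary objective. Separate rhos give a descriptive order without valid uncertainty for the differences.

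At the design's own value of 0.30 for all four markers, 28% to 48% of trials would show a mix of significant and non-significant markers, for inter-marker correlation 0.85 to 0.5. This is conditional: about 9% to 14% at a true correlation of 0.4 and about 1% at 0.5. It rests on multivariate normal data, equal correlations among markers and an inter-marker range that the article does not supply. At 85 patients, a difference of 0.2 from a marker at 0.3 is detected with moderate to high power, depending on that range. A difference of 0.1 mostly is not.

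**What to change.** In section 2.10, add:

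- For each of the six pairs of biomarkers, report the difference in Spearman rho in the same patients, with a 95% interval from a bootstrap that resamples patients.
- State the expected precision at 85 patients: half-width about 0.12 to 0.21 for an assumed inter-marker correlation of 0.85 to 0.5.
- Base any comparative statement on these intervals, not on which rho is significant.
- Present the intervals as exploratory. If any marker is to be declared superior, use simultaneous intervals over the six pairs, because unadjusted ones would falsely name a better marker in about 20% of trials when all are equal.

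The cost is a few lines of text and code on data already being collected, with no added patients or procedures. Simultaneous intervals are wider. The downside is that the honest conclusion may be that no marker is shown superior.

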**Methods and analysis:**

The RORSCHACH study is a prospective, multicenter, single-armed, non-blinded, non-controlled study evaluating cardiac biomarker release during elective aortic or mitral valve surgery and their correlation to perioperative myocardial damage as detected by MRI. Enrolled patients undergo routine monitoring including echocardiography, electrocardiography, cardiac biomarker analyses, and clinical symptom assessment preoperatively (within 24 h prior to surgery) and postoperative at predefined timepoints. LGE-cMRI is performed preoperatively and at least 5 days after surgery to clinically quantify any new myocardial damage. In total, 100 patients will be enrolled, whereby a drop-out rate of 15 % subsequently results in 85 patients necessary for final analysis. The primary endpoint is the correlation of the peak value of the respective biomarker with the amount of perioperatively induced myocardial damage quantified by LGE-cMRI.

**Discussion:**

The RORSCHACH trial will deliver the first comparative and quantitative information on the predictive value of the three classic cardiac injury markers used for the detection of new perioperative irreversible injury/MI in cardiac surgery.

**Study registration:**

Clinicaltrials.gov. NCT06066970. Registered on September 28th 2023.

## Introduction

1

Cardiac biomarkers are important components for diagnosing perioperative myocardial infarction (MI). However, their reliability as sole diagnostic indicators remains controversial [1]. Elevated levels of cardiac biomarkers, such as troponin I (TnI), troponin T (TnT), creatine kinase (CK), and its MB isoenzyme (CK-MB), are not exclusively linked to ischemic events [2,3]. Non-ischemic conditions, including renal insufficiency, neurological disorders, and even physical exertion from endurance sports, have been associated with increased biomarker release [[2], [3], [4], [5]], which means that the elevation of biomarkers may not automatically be translated to the presence of irreversible cell injury.

The use of the biomarkers for defining periprocedural MI in current trials has therefore sparked considerable controversy [[6], [7], [8]]. The biomarker elevation can complicate the differentiation between true ischemic myocardial injury and other contributing factors, thereby emphasizing the need for more comprehensive diagnostic approaches. Currently, there are different types of evidence searching for a more precise correlation between biomarkers kinetics and possible myocardial damage in consensus [9], guideline [10] or universal definition level [11].

Recently, novel imaging techniques (e.g. late gadolinium enhancement cardiac magnetic resonance imaging − LGE-cMRI) showed to have the potential to detect myocardial damage through surrogate indicators, providing valuable insights into early pathological changes and facilitating timely diagnosis and intervention. In light of these limitations, this study aims to investigate the relationship between the perioperative release of cardiac biomarkers and detectable myocardial damage through LGE-cMRI.

## Methods and analysis

2

### Overview of the study design

2.1

The RORSCHACH study is an investigator-initiated, prospective, multicenter, single-armed, non-blinded, non-controlled study. Adult patients undergoing elective aortic or mitral valve surgery will be considered for study participation. Enrolled patients will receive routine monitoring including echocardiography, electrocardiography, cardiac biomarker analysis, clinical symptom assessment at defined timepoints. LGE-cMRI is performed preoperatively (within 24 h before surgery) and at least 5 days after surgery. Cardiac Biomarker analyses, namely TnI, TnT, CK, and CK-MB, as well as LGE-cMRI analyses will be performed centrally at a Core Lab in Jena. A total of 100 patients including drop-outs are planned to be included. There are eight different participating sites in Germany, of which five a currently initiated (Fig. 1). All sites provide the necessary staff and equipment with regard to conducting LGE-cMRI.

**Fig. 1 f0005:**
[figure not shown]
Participating heart centers in Germany.

### Objectives

2.2

#### Primary objective

2.2.1

The primary objective of the study is to assess whether the perioperative releases of TnI, TnT, CK, and CK-MB correlate with myocardial damage, visualizable by LGE-cMRI. The primary endpoint is the correlation of the peak value of the respective biomarker with the amount of perioperatively induced myocardial damage quantified by LGE-cMRI.

#### Secondary objective

2.2.2

This study will also address further endpoints and questions that, while not directly related to the primary study objective, are clinically highly relevant with regard to perioperative mortality and morbidity. These secondary endpoints comprise of the perioperative complications mentioned in section *Possible Complications and/or Risks*.

### Study population

2.3

The study population comprises of adult patients undergoing elective aortic or mitral valve surgery. Eligible patients must not be diagnosed with coronary heart disease to minimize the probability of myocardial damage due to coronary pathology or coronary complications.

#### Inclusion criteria

2.3.1

•Indication for aortic or mitral valve surgery•Written informed consent•Age ≥ 18 years

#### Exclusion criteria

2.3.2

•Presence of coronary artery disease (excluded within the last 6 months)•Allergy to gadolinium•Non-MRI-competent (metal) implants (e.g. cardiac pacemaker, joint prothesis)•Cochlear implant•Deep brain stimulation•Individual factors excluding the performance of an MRI (e.g. claustrophobia of the patient)•Significantly reduced renal function (GFR < 30 ml/min)•Perioperative complications that may lead to myocardial damage•Need for extension of surgery•Pregnancy or lactation

### Obtaining informed consent

2.4

The nature of the study must be explained to each subject followed by written informed consent prior to enrollment. Obtaining written informed consent will then be carried out according to the Declaration of Helsinki and ICH-GCP E6. All patients enrolled must be capable of understanding the study design adequately and giving written informed consent by themselves. Study inclusion by means of a legal representative is not permitted.

### Screening

2.5

Patient recruitment is carried out as part of the elective patient treatment. Patients are assigned on the basis of the indication for surgery (isolated aortic or mitral valve surgery). The exclusion of stenosing coronary heart disease by means of coronary angiography or coronary CT must have been performed preoperatively within the last 6 months. Since the RORSCHACH study is single-armed and non-blinded no randomization and blinding procedures are performed.

### Frequency and scope of visits

2.6

Table 1 and Fig. 2 show the frequency and scope of trials’ visits. The study duration for the individual patient is at least 6 days comprising of a preoperative day and 5 days post surgery. After day 5 all diagnostics and sampling have been carried out and the patients’ end of study is reached. There will be no follow-up period.

**Table 1 t0005:** Frequency and scope of RORSCHACH visits.

Timepoint	Pre-OP	0 h	4 h	8 h	12 h	24 h	48 h	72 h	96 h	120 h
Medical history / baseline	X	-	-	-	-	-	-	-	-	-
Informed consent	X	-	-	-	-	-	-	-	-	-
Checking inclusion and exclusion criteria	X	-	-	-	-	-	-	-	-	-
Checking perioperative complications leading to myocardial damage (immediate end of study)		X	X	X	X	X	X	X	X	X
Physical examination	X									
LGE-cMRI	X	-	-	-	-	-	-	-	-	X
ECG	X	X	X	X	X	X	X	X	X	X
TTE (eventually TEE)	X	(-)	X	(-)	(-)	(-)	(-)	(-)	(-)	X
Sampling for central laboratory (TnI, TnT, CK, CK-MB)	X	X	X	X	X	X	X	X	X	X
Recording complications	-	X	X	X	X	X	X	X	X	X

(-): no TTE (eventually TEE) planned, only performed in case of possible myocardial damage. CK, creatine kinase; CK-MB, creatine kinase muscle-brain isoenzyme; ECG, electrocardiography; h, hour; LGE-cMRI, late gadolinium enhancement cardiac magnetic resonance imaging; OP, operation; TEE, transesophageal echocardiography; TnI, Troponin I; TnT, Troponin T; TTE, transthoracic echocardiography.

**Fig. 2 f0010:**
[figure not shown]
Study timeline. AV, aortic valve; ECG, electrocardiography; h, hour; ICU, intensive care unit, LGE-cMRI, late gadolinium enhancement cardiac magnetic resonance imaging; MV, mitral valve; OP, operation; TEE, transesophageal echocardiography; TTE, transthoracic echocardiography; VP, venipuncture.

Enrolled patients undergoing isolated aortic or mitral valve surgery receive routine monitoring according to local routine including clinical symptom assessment, transthoracic echocardiography (TTE), 12-channel electrocardiography (ECG), and preoperative laboratory diagnostic. Transesophageal echocardiography (TEE) is only performed if medically indicated. Diverging from clinical routine patients undergo blood sampling for assessment of cardiac biomarkers (TnI, TnT, CK, CK-MB) as well as LGE-cMRI. Isolated aortic or mitral valve surgery is conducted according to local clinical standards.

Further diagnostic measures are done postoperatively as indicated above. Blood sampling for cardiac biomarkers and ECG are performed at patients’ arrival on intensive care unit (ICU) (0 h) as well as after 4 h, 8 h, 12 h, 24 h, 48 h, 72 h, 96 h, and 120 h. Echocardiography is done fast-track (4 h − analysis of left ventricular ejection fraction and possible wall motion abnormality) and in a detailed manner before discharge (120 h). Patients receive one additional LGE-cMRI after at least 120 h. From surgery to the patients’ individual end of study participation complications are monitored and documented continuously.

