### Possible complications and/or risks

2.9

No additional complications and/or risks for the patients during study participation are expected. Based on the nature of the study and its regulatory classification no safety reporting is required. Nevertheless, for secondary endpoint assessment as well as due to possible study exclusion of patients after enrolment the focus will be on the documentation of the following events:odeath.oMI with angiographic evidence of coronary ischemia.ostroke.opostoperative AV block II° or III° and need for pacemaker implantationore-thoracotomy due to bleeding and/or cardiac tamponade.opostoperative delirium.orespiratory insufficiency with need for re- or protracted invasive ventilationopneumonia.oacute renal failure with indication for dialysis.oallergic reaction to gadolinium (of any degree).operioperative complications resulting in study exclusion (coronary complications, extension of the operation beyond isolated heart valve operation, prolonged extracorporeal circulation e.g ECMO application, resuscitation).

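### Gadolinium reactions are a secondary-endpoint event, but complication recording starts at surgery and so leaves out the first of the two study scans

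*Protocol article*

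**What the plan says.** - **The event.** Section 2.9 (Possible complications and/or risks) lists the events to be documented, "for secondary endpoint assessment as well as due to possible study exclusion of patients after enrolment the focus will be on the documentation". A gadolinium allergy of any severity is one of the 11 items.
- **Its status.** Section 2.2.2 (Secondary objective) states: "These secondary endpoints comprise of the perioperative complications mentioned in section", and the section it names is 2.9.
- **The exposures.** Section 2.1 (Overview of the study design): "LGE-cMRI is performed preoperatively (within 24 h before surgery) and at least 5 days after surgery". Section 2.6 (Frequency and scope of visits) repeats the second: "Patients receive one additional LGE-cMRI after at least 120 h".
- **The recording window.** Section 2.6, text below Fig. 2: "From surgery to the patients’ individual end of study participation complications are monitored and documented continuously". In Table 1 the row "Recording complications" has a dash at Pre-OP and an X at every time point from 0 h (arrival on ICU) to 120 h. The LGE-cMRI row has an X at Pre-OP and at 120 h.
- **A general statement.** Section 2.13 (Methods against bias) has possible outcomes documented in the CRF at every visit. It names neither the Pre-OP visit nor gadolinium.

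**The concern.** A window that opens at surgery suits the other listed events, which arise during or after the operation. It does not suit a contrast reaction, because one of the two contrast injections comes before surgery. A site that follows Table 1 and the section 2.6 text would have no instruction to enter a first-scan reaction as a complication, although sections 2.2.2 and 2.9 make such a reaction part of a secondary endpoint.

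What is at stake is the completeness of that one count. A reported number of gadolinium reactions would look as if it covered both scans while the recording rule covered only the second. Nothing in the stated schedule would let a reader separate the two.

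**Working it through.** The plan gives no figure for this point, so the check sets exposure times against recording times and then counts planned exposures.

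**Step 1. Timing, from Table 1 and the section 2.6 text**

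| | Pre-OP | 0 h to 96 h | 120 h |
|---|---|---|---|
| LGE-cMRI | X | dash | X |
| Recording of complications | dash | X | X |

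The dash in the Pre-OP cell is an entered value. Elsewhere in the table the plain dash clearly means not done: medical history and informed consent carry it at every time point after Pre-OP. The running text gives the same start point, so table and text agree with each other and both disagree with the event list.

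**Step 2. Each scan against the window**

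- First scan: within 24 h before surgery. The window opens at surgery. Outside.
- Second scan: at 120 h or later. The 120 h column has an X for both rows, and the text runs recording to the individual end of participation, which section 2.6 places after day 5, when all diagnostics are done. Inside.

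**Step 3. Share of planned exposures outside the window**

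Inputs: 2 planned scans per patient (section 2.1); 100 patients enrolled and 85 evaluable (section 2.11, Sample Size).

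Share outside = n first scans / (2 × n scans), if all n patients complete both:

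- n = 100: 100 / 200 = 50%
- n = 85: 85 / 170 = 50%

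The share does not depend on n under full completion. It counts exposures and not lost events, because the article gives no reaction rate.

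**The case against.** The best argument for the plan is section 2.13. Pre-OP is a column of the visit table, so an instruction to document outcomes at every visit could be read to include it. Section 2.9 also sets no start time for its list and says that the list serves possible exclusion after enrolment. This shows that the passages conflict, and that some sites may well record a first-scan reaction. It does not remove the conflict: one general sentence stands against a specific table cell and a specific start point.

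It is also fair to say that the study is exploratory and essentially descriptive, that section 2.9 requires no safety reporting, and that this is one of 11 items. That limits the weight of the point but not its correctness.

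Four stronger readings are tempting, and the documents do not support them:

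- *The window closes at the second injection.* No passage says so. Scan and recording share the 120 h column, and recording runs to the end of participation. How long patients are observed after that scan is left open, which a condensed article may leave to the full protocol.
- *54% of exposures go unrecorded.* That figure is 100 / (100 + 85) = 100 / 185. It assumes that all 100 patients have the first scan and exactly 85 have the second. Section 2.11 gives 85 as the evaluable number and does not say when drop-outs occur.
- *An unrecorded first reaction endangers the patient at the second scan.* The CRF is a research record. Nothing suggests that sites would rely on it in place of the hospital chart, and gadolinium allergy is itself an exclusion criterion.
- *The risk statement is contradicted.* Section 2.9 says "No additional complications and/or risks for the patients during study participation are expected", while section 2.6 says "Diverging from clinical routine patients undergo blood sampling for assessment of cardiac biomarkers (TnI, TnT, CK, CK-MB) as well as LGE-cMRI". A statement about what is expected, followed at once by a list of events to document, is not a contradiction. Rewording it would be a matter of preference.

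**Conclusion.** The point holds as an inconsistency between the event list and the recording window. Under the two specific entries in section 2.6, reactions to the first scan are not recorded as complications, so a secondary-endpoint component is incomplete by design. Reactions at the second scan can be recorded.

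The size is one of two planned exposures per patient, or 50% if all patients complete both scans. This rests on reading the Table 1 dash as not done and on giving the specific entries precedence over the general sentence in section 2.13. The number of reactions missed cannot be estimated from the article.

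Severity is minor. The primary correlation, the sample size and the biomarker analyses are unaffected.

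**What to change.** Reconcile sections 2.6, 2.9 and 2.13:

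1. In Table 1, change the Pre-OP cell of the complications row from a dash to an X, with a footnote limiting it to gadolinium reactions.
2. In the section 2.6 text, keep the start at surgery for the other events and start documentation of gadolinium reactions at the first study gadolinium injection.
3. Record in the CRF which scan each reaction followed, and report the counts by scan with the number of patients scanned as denominator.

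The cost is one table cell, one sentence and one extra CRF field. The information comes from existing radiology and ward records and needs no added visit or procedure. For patients already scanned, first-scan reactions could be sought in those same records.
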